#### Psycho-education (session 1)

In the first session, the participants will be provided with psycho-educational information about stress based on Lazarus’ transactional model of stress [35], that includes emotion-focused and problem-focused coping strategies. Following a video introduction to the basic information about stress and coping methods, an interactive quiz will be presented to equip participants with general knowledge of the most appropriate coping strategies for common problem situations. The participants will identify their personal stressors and define their goals and motivation during the training. Furthermore, participants will be asked to choose one positive activity each day.

#### Problem solving (session 2–3)

In sessions 2 and 3, the participants will work on their problem-solving skills. This module is based on problem solving therapy [43]. The participants will learn a systematic six-step problem-solving method that can be applied to their individual problems. This method has already been adopted in other web-based studies [13,44]. Typical scenarios involving work-related stress will be presented. The participants will fill out their own six-step procedures and use their personal solution in the time between the sessions. In session 3, the participants will have the opportunity to either work on the same problem as in the previous session or choose a new problem.

#### Emotion regulation (session 4–6)

In sessions 4 to 6, the participants will work on the emotion regulation module. The emotion regulation techniques are based on the Affect Regulation Training (ART) [37,45] and include muscle and breathing relaxation, acceptance and tolerance of emotions and effective self-support. ART has been shown to be effective as additional treatment component in cognitive-behavioral treatment for depression [37] and also as stand-alone intervention in at risk-populations (i.e., police officers) [46]. In each session, one strategy will be taught, and the participants will practice that strategy with a 15-minute audio file according to the instruction of an expert. The techniques will be introduced using examples of typical emotional reactions related to work contexts. Video files explaining the psychological background will be displayed. The participants will be asked to listen to the appropriate 15-minute audio file on a daily basis and will be provided with downloadable mp3 files.

#### Plan for the future (session 7)

In the last session, the participants will be asked to reassess their goals for the training. Furthermore, they will identify their personal warning signs for stress. Additionally, they will be asked to strengthen something important in their lives and write a letter to themselves about how they imagine their life will be after four weeks of applying the stress-management methods they have been trained in.

#### Optional booster session

Four weeks after completing the training, the participants will be given the option of completing a booster session and evaluating their training progress. They will be given the opportunities to evaluate the letter they wrote to themselves in the last training session, reassess their goals and make plans to continue to include positive activities in their daily lives.

#### Additional information

At the end of sessions 2 to 6, information and exercise sections about common stress-related topics will be provided to enhance the recognition value of the stress-management training. These sections are optional and will not be part of the main intervention. These sections will cover the following topics: time management, rumination and worrying, psychological detachment from work, sleep hygiene, rhythm and regularity of sleeping habits, nutrition and exercise, organization of breaks during work, and social support.

#### Text message coach

If desired, participants will receive automatic motivational text messages and small exercises on their mobile phones. These messages will support the participant in transferring the exercises of the training into their daily lives (e.g., short relaxation exercises: “Relax your muscles in your hands and arms for 3 seconds now. Follow your breathing and each time you breathe out, relax a little more“). The participants will have the opportunity to choose between “light coach” (one text message every other day) and “intensive coach” (2–3 text messages every day) options.

#### eCoach support

Within 48 hours, the participants will receive personalized written feedback on the exercises they have completed in each session from an eCoach. The eCoaches are psychologists and trained master’s-level psychology students and will follow guidelines about the feedback process that are defined according to the standardized manual for the intervention. The eCoaches will send reminders in cases in which the participants do not complete one session within 7 days. The training itself, and the communication between the participant and the eCoach will take place in a secured web-based platform (AES 256-bit encryption). The participants will have access to the platform based on their email-addresses and self-designated passwords.

### Primary and secondary outcomes

Primary outcome will be perceived stress. In secondary analyses, we will explore the effects of depression, anxiety, emotional exhaustion, emotion regulation, attitudes toward seeking professional psychological help, work engagement, psychological detachment, insomnia severity, worrying, and absenteeism/presenteeism. Economic analyses will be conducted assessing cost-effectiveness and cost-utility from a societal perspective including the costs of all types of health services and the costs that stem from productivity losses.

### Outcome measures

#### Perceived stress

The German version of the ten-item-Perceived Stress Scale (PSS-10) [47,48] will be used as a primary outcome measure. The PSS is “the most widely used instrument for measuring perceived stress” [47] and assesses the degree to which people perceive their lives as stressful, particularly regarding how “unpredictable, uncontrollable and overloading respondents find their lives” [49]. Cronbach’s alphas range for this scale from .78 to .91 [49]. The scale is based on Lazarus’ transactional model of stress and, therefore, fits well with the theoretical basis of the intervention. Participants in this study will be asked to answer questions relating to the past week as opposed to the past month to avoid confounding with the training period. Similar procedures have been adopted in previous studies [48].

#### Depression

Depressive symptoms will be measured with the German version of the Center for Epidemiological Studies’ Depression Scale (CES-D) [50,51]. This frequently used self-report instrument consists of 20 items that are answered on a four-point Likert scale referring to the previous week. Total scores range from 0 to 60. The internal consistency of this measure has been found to be α = .89 [51].

#### Anxiety

Anxiety symptoms will be measured with the German version of the anxiety subscale of the Hospital Anxiety and Depression Scales (HADS) [52,53]. This subscale contains seven items related to the previous week. Each item is scored from 0 to 3; thus, the scores range from 0 to 21. The HADS has been shown to have a high internal consistency of α = .80 [53].

#### Emotional exhaustion

The German version of the Maslach Burnout Inventory (MBI-GS-D) [54,55] will be used to measure emotional exhaustion, the basic stress dimension of burnout. This commonly used self-report instrument consists of five items and uses a six-point Likert-type scale anchored by 1 = “never” and 6 = “very often”. The internal consistency of this subscale was α = .85 in a German sample [56].

#### Emotion regulation

To assess emotion regulation skills we will use the German Emotion Regulation Skills Questionnaire (ERSQ-27 and ERSQ-ES) [57,58]. The subscales of acceptance, emotional self-support and comprehension will be included to assess the usage of general emotion regulation skills during the previous week and measured on a five-point Likert-type scale (ranging from “not at all” to “almost always”). Each scale is comprised of three items. The overall Cronbach’s α of the ERSQ-27 was .90 in a community-based sample, and for the subscales of acceptance, emotional self-support and comprehension .68, .72 and .73, respectively [57]. Furthermore, the subscale “general distress” from the emotion-specific version of the ERSQ (ERSQ-ES) [58] will be used to assess the regulation of stress. Therefore, the general distress subscale containing 12 items will be applied to assess constructive coping with stress and tension within the last week on a five-point Likert-type scale (ranging from “not at all” to “always”). This subscale has a high internal consistency of α = .85 [58].

#### Attitudes toward seeking professional psychological help

We will measure the influence of attitudes toward mental health care service utilization with the ten-item Attitudes Toward Seeking Professional Psychological Help Scale – Short Version (ATSPPHS-SF) [59]. The items of this scale are answered on a four-point Likert scale and result in total scores of 0–30; higher scores indicate more positive attitudes. In a normative sample, this scale showed an adequate internal consistency (α = .84).

#### Work engagement

The Utrecht Work Engagement Scale (UWES) [60] assesses work engagement defined as a “positive, fulfilling, work-related state of mind that is characterized by vigor, dedication, and absorption” [61]. This scale has nine items, and the internal consistency of the total score is α = .91.

#### Psychological detachment

Psychological detachment from work will be measured with a subscale of the Recovery Experience Questionnaire (REQ) [62]. This subscale contains four items that are rated on a five-point Likert scale. The internal consistency of this subcscale is α = .85 [62].

#### Insomnia severity

Insomnia severity will be measured with the Insomnia Severity Index (ISI) [63,64]. This seven-item scale measures the nature, severity and impact of insomnia and is rated on a five-point Likert scale. The total score indicates overall insomnia severity and ranges from 0 to 28. This scale has been validated as a web-based measure [65]. Internal consistency has been found to be Chronbach’s α =.90 and .91 [66].

#### Worrying

We will use the ultra-brief three-item version of the Penn State Worry Questionnaire (PSWQ) [67,68] to assess worrying. Each item is answered on a seven-point scale. We have adapted the questionnaire to encompass the previous week based on the three items of the Penn State Worry Questionnaire-Past Week (PSWQ-PW) [69,70]. Total scores range from 0-18. The psychometric properties of the English ultra-brief version are similar to the standard English 16-item version (Cronbach’s α = .85 compared to α = .91 for the standard version) [68] and the German version of the PSWQ-PW.

#### Quality of life

We will use the Short Form 12 (SF-12) [71] and the EuroQol (EQ-5D) [72] to assess quality of life. The SF-12 [71] covers eight health domains (physical functioning, role limitations, pain, general health perception, vitality, mental health, emotional role and social functioning) and allows for the calculation of two sum scores for physical and mental health. We will also use the EQ-5D which is a widely applied, valid and reliable measurement of quality of life and consists of five items related to mobility, self-care, common activities, pain/discomfort and anxiety/depression. Furthermore, this measurement contains a visual analogue scale concerning health state.

#### Cost measures

The economic evaluation will be conducted from a societal perspective; thus, we will include direct medical (e.g., medicine), direct non-medical (e.g., parking) and indirect costs (e.g., productivity loss) [73] over the previous three months. We have adapted the Trimbos and Institute of Medical Technology Assessment Cost Questionnaire for Psychiatry (TiC-P) [74] for application to the German health care system.

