### Procedure

Participants will be recruited from the general working population via mass media (e.g., newspaper articles, television) between March and October 2013. Moreover, a major health insurance company (BARMER GEK) will support the recruitment process within their occupational health management program. On an open access website (http://www.geton-training.de) the interested people will be able to sign up to participate with an email-address. Applicants will receive further informational material concerning the study conditions and the training and will be asked to provide an email-address and a first and last name (which can be pseudonyms if desired) to participate. Afterwards, a link to the screening questionnaire will be sent. Applicants who are eligible for participation will be required to provide their informed consent and fill out the online baseline questionnaire. Subsequently, these participants will be randomly allocated to either the intervention or the control group. Participants will be informed of the outcome of the randomization and participants in the intervention group will receive immediate access to the GET.ON Stress training. Assessments will be scheduled at seven weeks and six months after randomization for both groups. However, the participants in the control group will receive the login data required to complete the training six months later than the intervention group. An extended follow-up for the intervention group is scheduled 12 months post-randomization.

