### Intervention

The web-based GET.ON Stress intervention is based on two main components: problem solving and emotion regulation. The intervention consists of seven sessions composed of modules for psycho-education (session 1), problem solving (sessions 2–3), emotion regulation (sessions 4–6) and plan for the future (session 7) (see Table 1). Each session can be completed in approximately 45–60 minutes and consists of general information, examples related to work, interactive exercises, quizzes, audio and video files, and downloadable work sheets and mp3 files. We will recommend to log in once or twice a week and to fill out a short daily stress diary. Depending on the module, further homework will be assigned. Using responsive web-design, participants can follow the program on the internet, a tablet or mobile phone. An integrated read-aloud function allows participants to follow the lessons in an audio-narrated way.

**Table 1 T1:** Content of the GET.ON stress training

**Session**	**Intervention content**	
1	Psycho-education	
2	Problem solving I	(Learning Phase)
3	Problem solving II	(Maintenance Phase)
4	Emotion regulation I	(Muscle- and breathing relaxation)
5	Emotion regulation II	(Acceptance and tolerance of emotions)
6	Emotion regulation III	(Effective self-support in difficult situations)
7	Plan for the future	

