#### Other measurements

Other measurements include demographic variables (e.g., age, gender, occupation etc.), the Effort Reward Imbalance Questionnaire – Short Form (ERI-SF) [75], the hope of improvement subscale of the German Patient Questionnaire on Therapy Expectation and Evaluation (PATHEV) [76] (adapted to the online training context), the German version of the Client Satisfactory Questionnaire (CSQ-8) [77,78] (adapted to the online training context), and a German questionnaire on the negative effects of psychotherapy (Ladwig, I., Rief, W., & Nestoriuc, Y.: Hat Psychotherapie auch Nebenwirkungen? Entwicklung des Inventars zur Erfassung Negativer Effekte von Psychotherapie (INEP) [Does psychotherapy have side effects? Development of an Inventory of Negative Effects of Psychotherapy (INEP)], submitted); adapted to the online training context). Approximately 30 minutes will be required to complete all questionnaires. For an overview of all outcome measures, see Table 2.

**Table 2 T2:** Outcome measures

	**T0**	**T1**	**T2**	**T3**	**T4**
					
Perceived Stress Scale	✔	✔	✔	✔	✔
Center for Epidemiological Studies Depression Scale	-	✔	✔	✔	✔
Hospital Anxiety and Depression Scales – Anxiety	-	✔	✔	✔	✔
Maslach Burnout Inventory – Emotional Exhaustion	-	✔	✔	✔	✔
Emotion Regulation Skills Questionnaire – Comprehension/Acceptance/Self-Support	-	✔	✔	✔	✔
Emotion Regulation Skills Questionnaire – General Distress	-	✔	✔	✔	✔
Attitudes Toward Seeking Professional Psychological Help Scale	-	✔	✔	✔	✔
Utrecht Work Engagement Scale	-	✔	✔	✔	✔
Recovery Experience Questionnaire – Psychological Detachment	-	✔	✔	✔	✔
Insomnia Severity Index	-	✔	✔	✔	✔
Penn State Worry Questionnaire – Ultra Brief	-	✔	✔	✔	✔
Trimbos/iMTA Questionnaire for Costs associated with Psychiatric Illness	-	✔	-	✔	(✔)
Quality of Life (EuroQol, SF-12)	-	✔	-	✔	(✔)
Demographic Variables Questionnaire	✔	-	-	-	-
Effort Reward Imbalance Questionnaire – Short Form	-	✔	-	-	-
Patient Questionnaire on Therapy Expectation and Evaluation (Online-Training)	-	✔	-	-	-
Client Satisfactory Questionnaire	-	-	(✔)	-	-
Questionnaire on Negative Effects of Online Trainings	-	-	(✔)	(✔)	(✔)
Potential Dropout Reasons	-	-	(✔)	-	-

*T0* Screening, *T1* Baseline, *T2* 7 weeks, *T3* 6 months, *T4* 12 months.

Assessments: ✔ = intervention and control group, (✔) = intervention group only

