#### Economic evaluation

We will perform an economic evaluation from a societal perspective that includes all relevant costs and outcomes. A cost-effectiveness analysis and a cost-utility analysis will be conducted. For cost-utility analyses, quality-adjusted life years (QUALYs) will be calculated. A non-parametric boot-strapping method with 95% confidence intervals in percentiles will be used to assess differences between the intervention and control group. We will compare the intervention and control groups in terms of incremental costs and incremental effects. Towards this end, we will calculate the incremental cost-effectiveness ratio (ICER). We will use bootstrapping (5,000 times) to test the robustness of the ICER and to quantify the uncertainty in the ratios. The results will be shown in a cost-effectiveness plane and in a cost-effective acceptability curve. Additionally, the robustness of the base-case findings will be tested with a multi-way sensitivity analysis.

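### A three-month cost recall at baseline and 6 months leaves participant-reported costs for months 0–3 unobserved in both arms

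*Protocol article*

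**What the plan says.** The Cost measures section sets the recall. The adapted TiC-P asks about direct medical costs, direct non-medical costs and "indirect costs (e.g., productivity loss) [73] over the previous three months".

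Table 2 sets the schedule. The row "Trimbos/iMTA Questionnaire for Costs associated with Psychiatric Illness" has a dash at T0 (screening), a tick at T1 (baseline), a dash at T2 (7 weeks), a tick at T3 (6 months) and a bracketed tick at T4 (12 months). The legend reads "Assessments: ✔ = intervention and control group, (✔) = intervention group only".

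On timing, the Procedure section states "Assessments will be scheduled at seven weeks and six months after randomization for both groups" and "participants in the intervention group will receive immediate access to the GET.ON Stress training". Controls get their login six months later. The Intervention section adds "The intervention consists of seven sessions", with one or two log-ins a week recommended. An optional booster follows four weeks after completion.

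On scope, the Economic evaluation section states: "We will perform an economic evaluation from a societal perspective that includes all relevant costs and outcomes".

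**The concern.** A recall questionnaire measures a flow over a window that ends on the day it is completed. If the windows do not meet, the cost accrued between them is not recorded. Here recall length and schedule are both fixed in the article, and together they leave a gap straight after randomisation. That is when the training is meant to take place and when health-care use, absence or reduced productivity could first change.

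What is at stake is the incremental cost, and with it the ICER, the cost-effectiveness plane and the acceptability curve. Cost-effectiveness is a stated aim and hypothesis of the trial. The planned 5,000 bootstrap replicates resample observed costs, so they carry forward whatever is assumed for the missing months and cannot reveal an error in it. The randomised contrast cannot be rebuilt later, because controls gain access at six months.

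**Working it through.** The article gives no figure for cost coverage, so there is none to reproduce. The sample size of 264 does not enter this point.

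**Inputs.** Recall 3 months (Cost measures). TiC-P at 0 and 6 months in both arms and at 12 months in the intervention group only (Table 2 and legend). Training access at month 0 (Procedure). Seven sessions at one or two log-ins a week (Intervention). Booster four weeks after completion (Optional booster session).

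**Windows covered** (visit minus 3 months, up to the visit):

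| Visit | Arms | Months covered |
|---|---|---|
| T1 | both | −3 to 0 (before randomisation) |
| T3 | both | 3 to 6 |
| T4 | intervention only | 9 to 12 |

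Within the two-arm period of 0 to 6 months, 3 of 6 months (50%) are observed. Months 0–3 are not observed in either arm.

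**Where the training falls** (assuming one session per log-in). At one a week, seven sessions end at week 7, or 7 × 12/52.18 = 1.6 months. At two a week they end at 3.5 weeks, or 0.8 months. At the weekly pace the booster comes at week 11, or 2.5 months. All of these lie inside the gap.

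**What each way of filling the gap assumes.** Let D1 and D2 be the true between-arm cost differences in months 0–3 and 3–6. The target is D1 + D2.

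- Omit the quarter: estimates D2; error −D1.
- Double months 3–6: estimates 2·D2; error D2 − D1.
- Interpolate linearly between the T1 and T3 quarters: the total is 0.5·T1 + 1.5·T3. The expected T1 difference is zero under randomisation, so this estimates 1.5·D2; error 0.5·D2 − D1.

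Each error is zero only under a specific relation between D1 and D2 (D1 = 0, D1 = D2, or D1 = 0.5·D2), and the planned data cannot test any of them.

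**Precision, for illustration only.** Assume equal quarterly variances and one common between-quarter correlation r. Neither is given in the article. In units of the quarterly variance, the fully measured half-year has variance 2 + 2r, doubling has 4, and interpolation has 0.25 + 2.25 + 1.5r = 2.5 + 1.5r.

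| r | SE ratio, doubling | SE ratio, interpolation |
|---|---|---|
| 0.3 | 1.24 | 1.07 |
| 0.5 | 1.15 | 1.04 |
| 0.7 | 1.08 | 1.02 |

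**Candidate repairs, coverage of months 0–6.**

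- TiC-P added at week 7 with the three-month recall unchanged: 1.6 + 3.0 = 4.6 of 6 months. Month 1.6 to month 3 stays open, and the new window overlaps the baseline one.
- TiC-P at week 7 since randomisation, then at 6 months since the last cost questionnaire: 6 of 6. The second recall is 26 − 7 = 19 weeks.
- TiC-P added at 3 months with the recall unchanged: 6 of 6.

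**The case against.** The best defence is that valuing an unobserved interval is analysis-plan business. EQ-5D is also taken only at T1 and T3, so QALYs already need an assumed path, and a multi-way sensitivity analysis is planned. This stands in part: the article does not prescribe a method, and a plan could choose one openly. It does not remove the gap. The article itself fixes both recall and schedule, and an analysis plan can only choose an assumption. Interpolated costs lean on a pre-randomisation quarter that cannot carry a treatment effect. The content of the sensitivity analysis is not stated.

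A reader might infer several stronger things that the article does not support:

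- *That costs are collected after randomisation only at 6 months.* Table 2 also has a 12-month TiC-P. It does not help, being one-armed and covering months 9–12.
- *That the training itself goes uncosted.* The gap concerns participant-reported costs. eCoach time and platform costs could come from provider records. The article does not name the source, which it may leave to the full protocol.
- *That the ICER will set three months of cost against six months of effect.* The article does not say so and does not fix the costed horizon.
- *That precision necessarily suffers by 8–24%.* That range belongs to doubling under assumed correlations and equal variances. Interpolation gives about 2–7%.
- *That the absenteeism/presenteeism comparison fails.* Table 2 lists no separate instrument for it, so it appears to rest on the same questionnaire. Comparing the arms at T3 remains a valid randomised comparison, for months 3–6 only.

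**Conclusion.** The point holds for participant-reported health-care, non-medical and productivity costs: half of the randomised six months is unobserved in both arms, which conflicts with the claimed completeness of the economic evaluation. The 50% figure follows directly from the article if the three-month recall applies at every administration and visits occur on schedule. That the training lies wholly within the gap also assumes the recommended pace; slower participants would carry some of it into the observed window.

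A six-month incremental cost will be biased if the cost effect in months 0–3 departs from whatever is assumed for it. The article gives no basis for the size or direction of that bias, and none is claimed here. The matter is confined to the economic evaluation and the width of the absenteeism/presenteeism window. The primary PSS-10 comparison and its sample size are untouched.

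**What to change.** Make the cost windows contiguous from randomisation to 6 months in both arms, and state that period as the costed horizon. There are two ways:

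1. Add the online TiC-P at T2 with recall since randomisation, and set the T3 recall to since the last cost questionnaire. The recall wording must change along with the schedule. This uses an assessment that already takes place. The cost is a few minutes of respondent burden and a recall of about 19 weeks at T3 instead of three months. That is a real loss for items such as medication, travel expenses and lost productivity.
2. Add one online TiC-P at 3 months and keep the three-month recall. This avoids the long recall but needs an additional contact in both arms.

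If the schedule cannot change, there are two fallbacks. One is to limit the costed horizon to months 3–6 and label the result so. The other is to state the extrapolation assumption for months 0–3 in advance and vary it in the planned multi-way sensitivity analysis. In either case the statement that all relevant costs are included should be dropped, and absenteeism/presenteeism results should be reported as covering months 3–6. These fallbacks cost nothing in data collection but leave the first quarter unknown.
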